## Abstract

**Background:**

Antibodies blocking programmed cell death 1 (PD-1) have encouraging responses in patients with metastatic melanoma. Response to anti-PD-1 treatment requires pre-existing CD8+ T cells that are negatively regulated by PD-1-mediated adaptive immune resistance. Unfortunately, less than half of melanoma tumours have these characteristics. Combining anti-PD-1 treatment with other immunomodulating treatments to activate CD8+ T cells is therefore of vital importance to increase response rates and long-term survival benefit in melanoma patients. Both preclinical and retrospective clinical data support the hypothesis that radiotherapy increases the response rates to anti-PD-1 treatment by stimulating the accumulation and activation of CD8+ T cells in the tumour microenvironment. Combining radiotherapy with a PD-1 blocking antibody might therefore increase response rates and even induce long-term survival. The current phase II study will be testing these hypotheses and aims to improve local and distant tumour responses by exploiting the pro-immunogenic effects of radiotherapy in addition to anti-PD-1 treatment.

**Methods:**

The trial will be conducted in patients with metastatic melanoma. Nivolumab or pembrolizumab, both antibodies that target PD-1, will be administrated according to the recommended dosing schedule. Prior to the 2nd cycle, radiotherapy will be delivered in three fractions of 8 Gy to the largest FDG-avid metastatic lesion. The primary endpoint is the proportion of patients with a partial or complete response in non-irradiated metastases according to RECIST v1.1. Secondary endpoints include response rate according to immune related response criteria, metabolic response, local control and survival. To identify peripheral blood biomarkers, peripheral blood mononuclear cells and serum samples will be collected prospectively before, during and after treatment and subjected to flow cytometry and cytokine measurement.

**Discussion:**

The current phase II trial aims at exploring the suggested benefits of combining anti-PD-1 treatment and radiotherapy. The translational focus on immunologic markers might be suitable for predicting efficacy and monitoring the effect so to improve patient selection for future clinical applications.

*ClinicalTrials.gov Identifier* NCT02821182

## Background

Patients with metastatic melanoma had a median overall survival of only 6–9 months [1] until a breakthrough was achieved with novel immunomodulatory agents blocking specific immune checkpoints. Immune checkpoints, such as cytotoxic T lymphocyte-associated antigen 4 (CTLA-4), PD-1 and programmed cell death 1 ligand (PD-L1), are negative regulators of the immune system, that play critical roles in maintaining self-tolerance and modulating immune responses to protect normal tissue from immune collateral damage. Inhibition of these immune checkpoints by CTLA-4 blocking agents and anti PD-L1 antibodies is therefore able to reactivate T cells and restore anti-tumour immunity, resulting in impressive efficacy in patients with metastatic melanoma [2].

For these patients, antibodies targeting PD-1 have shown superior responses than those seen with CTLA-4 blocking agents, with response rates of 34% compared to 11% respectively [3]. Unfortunately, there still remain a substantial number of patients that do not obtain any clinical benefit. It is hypothesized that anti-tumour responses are limited by other immune inhibitory mechanisms present in the tumour microenvironment (TME). Patients who do not respond to PD-1 blocking agents typically have an immune suppressive TME hampering the activation of CD8+ cytotoxic T cells (CTLs). These patients may require the addition of other therapies that enhance anti-tumour immunity or circumvent immune inhibition. Potential candidates include other immunotherapies and radiotherapy.

Radiotherapy has important effects on the immune system and is able to shift the balance from tumour immune evasion towards tumour control [4]. Additionally, the best tumour control and tumour immunity are more likely to be achieved with high dose per fraction radiotherapy [5, 6]. By using stereotactic body radiotherapy (SBRT) we are able to safely deliver such high doses of radiation very precisely in a small number of fractions. Preclinical evidence clearly indicates that SBRT increases response rates and long-term survival of anti-PD-1 treatment by stimulating the accumulation and activation of CD8+ CTLs in the TME [7–10]. Considering the delicate interplay between both modalities, we have chosen to investigate a specific combination sequence in which 1 cycle of anti-PD-1 treatment will precede SBRT. This sequence allows the creation of a more immune permissive TME in which radiotherapy can induce the release of multiple tumour antigens causing the activation of tumour-specific CD8+ CTLs. The subsequent cycles of anti-PD-1 treatment may further stimulate the effector function of activated CD8+ CTLs by blocking the engagement of PD-1 with its ligand PD-L1.

The current phase II trial aims at exploring the suggested benefits of this combination. Considering the toxicity of immune checkpoint inhibitors and their high economical cost, it is of utmost importance to identify patients who are likely to respond to these treatments beforehand. Unfortunately, there are currently no validated markers available to pre-identify responders, and even the effects of checkpoint inhibitors on circulating immune cells remain unknown. We therefore will monitor circulating immune cells and cytokine levels, to identify the mechanism of response and resistance to therapy. We recently demonstrated that low levels of plasmacytoid dendritic cells and high expression of indoleamine 2,3-dioxygenase (IDO) in the peripheral blood of melanoma patients confer a negative prognosis, independent of disease stage. Systemic IDO, PD-L1 and CTLA-4 expression were also interconnected [11]. We will specifically focus on the relevance of these markers, as they could help elucidate the counter-regulatory mechanisms and provide predictive information.

## Methods

### Objectives

#### Primary objective

The primary objective of this trial is to determine the response rate as per RECIST v1.1 of the combination of anti-PD-1 with SBRT.

#### Secondary objectives

Secondary objectives are to determine the immune-related response rate of the combination treatment, metabolic response, local control, progression free survival (PFS) and toxicity. We will also analyse circulating immune cells, cytokine levels and markers in tumour tissue (if feasible) during treatment.

### Trial design

This phase II trial assesses the response rates of the anti-PD-1/SBRT combination. Nivolumab or pembrolizumab will be administrated according to the recommended dosing schedule. Prior to the 2nd cycle, SBRT will be delivered (24 Gy in three fractions) to the largest (max. diameter of 5 cm) fluorodeoxyglucose (FDG)-avid metastatic lesion. Table 1 shows a general scheme of the trial.

**Table 1 Tab1:** General scheme of the trial

	Run-in period	Study period	Observation period	
SBRT		Three fractions of 8 Gy every other day		
Anti-PD-1 treatment	First cycle		Second cycle	Continuation

This trial uses a Simon two-stage optimal design, a design often used for phase II cancer clinical trials [12]. This design allows the assessment of the efficacy of a combination therapy in a relatively small number of patients.

### Outcome measures

#### Primary endpoint

Objective response rate of the non-irradiated metastases as determined by the response evaluation criteria in solid tumours (RECIST) v1.1 [13]. Response rate will be defined as the percentage of subjects achieving either a complete or partial response at 6 weeks after the start of anti-PD-1 treatment. Further follow up imaging will be performed at the discretion of the treating physician.

#### Secondary endpoints

Objective response rate of the non-irradiated metastases as determined by immune related response criteria (irRC) [14].Metabolic response of the irradiated and non-irradiated metastases based on the European Organization of Research and Treatment of Cancer (EORTC) 1999 criteria [15].Local control defined as the time between local irradiation and the moment the irradiated lesion shows an increase in size of ≥20%, according to the RECIST V1.1, confirmed by a consecutive assessment at least 4 weeks after first documentation.PFS: two types of PFS will be defined. One as the time from inclusion to documented disease progression according to RECIST v1.1 or death from any cause. The other as the time from inclusion to documented disease progression according to irRC or death from any cause.Acute and late toxicity due to the combination treatment will be scored using the Common terminology criteria for adverse events (CTCAE) version 4.0.

#### Exploratory endpoint

Immunologic responses assessed using peripheral blood samples and analysed with fluorescence-activated cell sorting (FACS) phenotyping, functional testing, ultra-performance liquid chromatography (UPLC) and enzyme-linked immunosorbent assay (ELISA). If feasible, immunologic responses will also be assessed on tumour tissue using IHC.

### Study population

Patients with metastatic melanoma who did not receive previous immunotherapeutic treatment and have at least two measurable extracranial lesions.

#### Inclusion criteria

Before patient registration, written informed consent must be given according to the International Council for Harmonisation of Technical Requirements for Pharmaceuticals for Human Use (ICH)/Good Clinical Practice (GCP), and national/local regulations.Histologically confirmed diagnosis of melanoma.Be able to provide tissue from an archival primary tissue sample or a newly obtained biopsy, for the evaluation of PD-L1 and other immune markers using immunohistochemistry (IHC).At least two extracranial measurable metastatic lesions per RECIST v1.1 and irRC. All radiological studies must be performed within 28 days prior to registration.Previous BRAF inhibitor when elevated lactate dehydrogenase (LDH) in patients with BRAF V600 mutations is allowed.Karnofsky Performance status >60.Age 18 years or older.Female participants of childbearing potential must be willing to use two methods of birth control or be surgically sterile, or abstain from heterosexual activity for the course of the study through 120 days after the last dose of study treatment.Female participants who are breastfeeding or plan to breastfeed should be instructed to discontinue nursing during treatment.Male participants must agree to use an adequate method of contraception starting with the first dose of study therapy through 120 days after the last dose of study treatment.Demonstrate adequate organ function defined as the following:Serum aspartate and alanine aminotransferase (AST and ALT) levels ≤2.5× upper limit of normal (ULN) or ≤5× ULN in patients with liver metastases.Serum total bilirubin ≤1.5× ULN or direct bilirubin ≤ULN for patients with total bilirubin level >1.5 ULN.Serum creatinine ≤1.5× ULN.Absolute neutrophil count ≥1000/mcL.Platelets ≥75,000/mcL.Hemoglobin ≥9 g/dL or ≥5.6 mmol/L.
No history of active autoimmune disease requiring systemic treatment within the past 3 months or documented history of clinically severe autoimmune disease, or syndrome that requires systemic steroids or immunosuppressive agents.Subjects who have had another malignancy should be disease-free for 5 years, or should have a history of completely resected non-melanoma skin carcinoma or successfully treated in situ carcinoma.No evidence of interstitial lung disease.No uncontrolled central nervous metastases and/or carcinomatous meningitis.No prior radiotherapy interfering with the radiotherapy treatment in the study.No concomitant therapy with interleukin-2, interferon, other immunotherapy regimens, chemotherapy, immunosuppressive agent or chronic use of systemic corticosteroids.No active infection requiring systemic therapy.No known history of human immunodeficiency virus.No known active Hepatitis B or Hepatitis C infection.Subjects should not have received a live vaccine within 30 days prior to start of study treatment.Subjects without a mental condition rendering the patient unable to understand the nature, scope and possible consequences of the study.Subjects who are likely to comply with the protocol; i.e. no uncooperative attitude, no inability to return for follow-up visits, and likely to complete the study.

### Evaluation and randomization

Patients must be restaged within 4 weeks prior to randomization with an 18F-FDG Positron emission tomography with X-ray computed tomography (PET/CT).

### Intervention

#### SBRT

Prior to the 2nd cycle of treatment, SBRT will be delivered to the largest FDG-avid metastatic lesion (max. 5 cm diameter). A total dose of 24 Gy will be delivered in two fractions with image-guided treatment verification and fractions will be separated >48 h and <96 h.

All patients will receive a CT simulation in supine position with 2 mm CT slice thickness through the tumour site. The planning simulation should cover the target and all organs at risk. A typical scan length should extend at least 10 cm superior and inferior beyond the treatment field borders. Support devices to increase patient comfort will be chosen depending on the tumour localisation. The isocenter will be determined on the CT-simulator with marking of laser lines on the patient. Imaging data will be transferred to the treatment planning system. For all lesions, the Gross Target Volume (GTV) will be defined as all visible tumour by combining iconographic and metabolic information. No additional margin will be added for microscopic spread of disease. The GTV will be expanded with 2–5 mm to the Planning Target Volume (PTV) to account for organ motion and setup error. Margins depend on the site irradiated with 2 mm margins for bony lesions, 3 mm for nodes and 5 mm for other sites. The type of organ at risk delineated depends on the localization of the metastasis. A Planning Organ at Risk Volume (PRV) expansion of 2–5 mm will be added for organs at risk (OAR) and dose constraints apply to this PRV. It is strongly recommended that dose constraints not be exceeded. If a dose constraint cannot be achieved due to overlap of the target with an organ at risk or its PRV, the total dose can be lowered in order to meet the constraint. Treatment will be prescribed to the periphery of the target (80% of the dose) covering the 90% of the PTV. Dose constraints of organ at risks will be in accordance with the recommendations of the American Association of Physicist in Medicine (AAPM) task group 101 report. In case of violation of constraints to the organs at risk, the prescription will be adapted accordingly.

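### The SBRT section prescribes 24 Gy in two fractions, while the abstract, the trial design text and Table 1 give three fractions, which is 8 Gy each

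*Protocol article*

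**What the plan says.** The protocol article states the fractionation in four places.

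- Abstract, Methods: "radiotherapy will be delivered in three fractions of 8 Gy to the largest FDG-avid metastatic lesion".
- Methods, Trial design (text): "SBRT will be delivered (24 Gy in three fractions", directed at the largest FDG-avid lesion up to 5 cm.
- Methods, Trial design, Table 1: "Three fractions of 8 Gy every other day".
- Methods, Intervention, SBRT: "A total dose of 24 Gy will be delivered in two fractions". On the interval, the same section requires more than 48 h and less than 96 h between fractions.

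The SBRT section also sets the margins, the prescription isodose and the organ-at-risk rules. Where a constraint cannot be achieved because the target overlaps an organ at risk, "the total dose can be lowered in order to meet the constraint". On the rationale, the Background says that "the best tumour control and tumour immunity are more likely to be achieved with high dose per fraction radiotherapy".

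**The concern.** The article gives two radiation schedules for the same treatment, and both cannot be right. The odd one out is in the section a radiation oncologist or physicist would consult to prepare a plan, and the same section a later group would use to reproduce the regimen.

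The number of fractions matters for three reasons. First, SBRT is what this trial adds to standard anti-PD-1 treatment, and the Background makes dose per fraction part of the reason to expect a benefit. Second, local control and the acute and late toxicity of the combination are secondary endpoints, and neither can be interpreted without knowing the schedule given. Third, the Discussion presents the trial as a step before randomized trials, so the regimen carried forward has to be unambiguous.

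**Working it through.** **Inputs from the protocol article**

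| Place | Total dose | Fractions | Dose per fraction |
|---|---|---|---|
| Abstract, Methods | 3 × 8 = 24 Gy | 3 | 8 Gy (stated) |
| Trial design, text | 24 Gy (stated) | 3 | 24 / 3 = 8 Gy |
| Trial design, Table 1 | 3 × 8 = 24 Gy | 3 | 8 Gy (stated) |
| Intervention, SBRT | 24 Gy (stated) | 2 | 24 / 2 = 12 Gy |

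The first three rows agree with one another. The fourth agrees on total dose only. The 12 Gy is derived by assuming equal fractions; the article does not print it.

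**Can anything in the article reconcile them?** The target lesion and the timing before cycle 2 are the same, so these are not two treatments. The permission to lower the total dose, or adapt the prescription, applies when an organ-at-risk constraint is not met; it does not describe a two-fraction schedule, and the sentence in question keeps the full 24 Gy. The spacing rule (more than 48 h and less than 96 h) can be applied to two or three fractions, so it does not fix the number. The Background favours a high dose per fraction but gives no figure, so it cannot choose between 8 and 12 Gy.

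**Size of the difference**

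Dose per fraction: 12 / 8 = 1.50, which is 50% higher at the same total.

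Biologically effective dose (BED) under the linear-quadratic model, for total dose D and dose per fraction d: BED = D × (1 + d / (α/β)). The article gives no α/β; the values 10 and 3 Gy are assumptions that show a range.

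| Assumed α/β | 3 × 8 Gy | 2 × 12 Gy | Ratio |
|---|---|---|---|
| 10 Gy | 24 × (1 + 8/10) = 43.2 Gy | 24 × (1 + 12/10) = 52.8 Gy | 1.22 |
| 3 Gy | 24 × (1 + 8/3) = 88 Gy | 24 × (1 + 12/3) = 120 Gy | 1.36 |

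**Would 24 Gy in two fractions be an equivalent way to give 3 × 8 Gy?** Solve for the two-fraction dose d with the same BED:

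- α/β = 10: 2d(1 + d/10) = 43.2 gives d = 10.52 Gy, total 21.05 Gy; 24 / 21.05 = 1.14.
- α/β = 3: 2d(1 + d/3) = 88 gives d = 10.09 Gy, total 20.17 Gy; 24 / 20.17 = 1.19.

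On these assumptions 24 Gy in two fractions is 14% to 19% above the matching total, so it is a more intense schedule and not a rescheduling of the same one.

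**After the correction:** with three fractions in the SBRT section, 24 / 3 = 8 Gy, and all four statements agree.

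**The case against.** The strongest reply is that this is a recoverable slip. The 8 Gy figure is printed twice, 12 Gy is printed nowhere, and three statements out of four agree, so a careful reader would infer 3 × 8 Gy. The article condenses a full protocol that is not shown; that protocol may be correct, and nothing in the article indicates that any patient is treated from the article or received two fractions. The statistical design is untouched, and the primary endpoint concerns non-irradiated lesions. The BED figures rest on α/β values from outside the document, and the contradiction is fully shown without them.

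Much of this stands. The likely reading is three fractions, harm is conditional on someone following the sentence as written, and the BED comparison only illustrates the size. It is also fair that the article cites its organ-at-risk constraint report without showing whether those constraints depend on the number of fractions, so a check of the constraint set is a precaution and no further finding.

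It does not remove the point. The article does not leave the schedule to the full protocol; it states it, in two incompatible ways, and the document alone cannot prove which is intended. Nor would the organ-at-risk rules necessarily catch the error: for a lesion away from critical organs, 2 × 12 Gy might meet every constraint and go through unadjusted.

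**Conclusion.** The concern holds: the SBRT section is wrong as written or, less plausibly, the other three statements are. At the same 24 Gy total, the stated number of fractions implies a dose per fraction 50% higher than the schedule given elsewhere, assuming equal fractions. With assumed α/β of 10 and 3 Gy, that corresponds to a BED 22% and 36% higher. It should be corrected before the document is relied on, because it is the prescription of the experimental treatment and bears on patient safety, on the toxicity and local-control endpoints, and on reproducibility. The two-stage sample size, its boundaries and the null response rate of 0.34 do not depend on it.

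**What to change.** Check the ethics-approved protocol. If it confirms the schedule in the abstract and Table 1, change the SBRT sentence to read: *A total dose of 24 Gy will be delivered in three fractions of 8 Gy.* While editing that sentence, align the spacing with Table 1: every other day is nominally 48 h, but the SBRT section requires more than 48 h.

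Two precautions go with it. Confirm that the organ-at-risk constraints in use are those meant for a three-fraction schedule, should the cited report distinguish them. If patients have already been treated, confirm the fractionation they received; nothing in the article suggests misdelivery.

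The cost is one corrected sentence, plus a short check of the constraint set and of any plans already delivered. No statistical quantity has to be recalculated.

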#### Systemic therapy

Anti-PD-1 treatment (nivolumab or pembrolizumab) will be administrated according to the recommended dosing schedule and continued until clinical progression. Patients may also discontinue protocol therapy when unacceptable toxicity is encountered. Administration of anti-PD-1 treatment should be withheld for a drug-related non-hematologic toxicity ≥grade 2 (excluding fatigue). The use of corticosteroids should be considered for management of immune-related adverse events. Once the patient has recovered to grade 0–1 consider increasing the dosing interval in subsequent cycles by 1 week. If the drug-related toxicity does not resolve to grade 0–1 within 12 weeks after onset of toxicity, discontinuation is recommended. Patients may also discontinue protocol in case of intercurrent illness, which would in the judgment of the investigator affect patient safety, the ability to deliver treatment or by request of the patient.

#### Evaluation of pre-treatment PD-L1 expression

A PD-L1 IHC assay using Merck mouse monoclonal antibody clone 22C3 will be performed on archival primary tissue sample or a newly obtained biopsy. Hematoxylin & eosin staining will be reviewed for confirmation of tumour presence.

### Follow-up

Patients will be seen before the start of each treatment cycle during the whole course of anti-PD-1 therapy. At each visit, a history and physical examination will be conducted with recording of the toxicity. For response evaluation, a 18F-FDG PET/CT will be performed at week 6. For further follow up, CT thorax, abdomen and pelvis or 18F-FDG PET/CT will be performed at the treating physician’s discretion until disease progression or treatment discontinuation. Additional imaging or laboratory investigations should be carried out at the discretion of the treating physician, based on findings in the history or physical examination.

